**Fig. 1 Fig1:**
[figure not shown]
Intervention conceptual method

## Method/design

### Design and participants

We will employ a SW-RCT with 30 outpatient SUD treatment clinics who serve approximately 2000 clients with OUD per year to test whether CARE improves treatment process quality and recovery outcomes over treatment as usual. The study will benefit from multiple sources of data to test study aims, including state administrative data, client-reported survey and eTPA8 data, and staff interview and survey data. Therefore, this will be a robust study of the implementation of a measures-driven QI approach for SUD treatment. Figure 2 shows the stepped-wedge design. Five clinics will start CARE every 6 months over 3 years; therefore, there are 6 steps, each with 5 clinics randomly assigned to 1 of the 6 steps.

**Fig. 2 Fig2:**
[figure not shown]
Stepped-wedge design

Clinics are being recruited from various regions in New York State—Long Island, New York City and its suburbs, the Hudson Valley, and central New York—that have diversity in population density, resources, and racial/ethnic representation. Inclusion criteria will be outpatient treatment programs licensed by the NYS Office of Addiction Services and Supports (NYS OASAS) with a minimum of 50 OUD clients per year. For-profit clinics will be excluded because of insufficient numbers within New York and differences in organizational culture. To recruit clinics, we first identified 77 eligible clinics based on our inclusion criteria using state administrative data. The study PIs and project director then invited these identified clinics via email to informational webinars about the study, emailed them information sheets describing the study, and reached out via personal emails to clinic leaders. NYS OASAS representatives from the study regions also sent informational emails to eligible clinics. To finalize recruitment, clinics who agree to participate will sign a clinic participation agreement form. Clinic randomization will be stratified by downstate (Long Island, New York City, and its suburbs) and rest-of-state (Hudson Valley and central New York). We will use the SAS PROC PLAN procedure to generate the randomization schedule; a data analyst at NYS OASAS not associated with the study will conduct this procedure to minimize bias.

### Intervention planning and pilot

This study was funded under a phased NIH award such that there was a 1-year developmental phase that was recently successfully completed, allowing for a second phase of funding for the SW-RCT described in this paper. During this 1-year developmental phase in 2019–2020, we conducted two stakeholder meetings, piloted CARE study components, tested and finalized the eTPA8 client-reported treatment progress tool, and created study materials and protocols. The stakeholder meetings were conducted to get input and feedback about the CARE intervention and included attendees from New York City, State and County agencies, clients with lived experience in SUD treatment, insurers, academic partners, and SUD treatment providers. A 3-month pilot was conducted in an outpatient clinic during which we tested components of the CARE intervention for feasibility, including engaging executive leadership, providing clinical and QI trainings, and using an external facilitator to engage clinic champions and a change team in a QI cycle. Focus groups were conducted to understand staff experiences during the CARE pilot, and intervention materials and protocols were finalized. Finally, we tested and finalized the eTPA8 client outcome monitoring tool by using cognitive testing procedures with pilot clinic clients and testing the tool on a web-based usability program [43–45]. We also asked pilot clinic staff for feedback on the eTPA8.

### Description of the CARE intervention

The overall goal of the multicomponent, clinic-level CARE intervention is to help SUD clinics make improvements in rates of OUD medication initiation and adherence, rates of 6-month retention, and recovery outcomes by providing training and implementing QI procedures with support from an external facilitator. The CARE intervention will be 1-year-long for each participating clinic. Guided by phased implementation models [46], ‘active’ intervention by the external facilitator will take place during the first 6 months (see Table 1). The second 6 months will be a sustainment phase in which clinics continue QI activities with limited facilitator support (e.g., troubleshooting). Guided by the i-PARIHS model, facilitators will support clinics in making adjustments to clinical and program procedures. They will tailor their approach to fit with each clinic’s workflow while addressing staff motivations and resources and attending to the inner and outer context of each clinic.

**Table 1 Tab1:** CARE intervention components during 6-month active phase

CARE component	Rationale	Execution	Target
Training/tools on OUD medications, shared-decision making, and person-centered care	Increase knowledge, skills, and, attitudes about evidenced-based practices to improve client outcomes	1-h, interactive web-based trainings; moderated discussion with external facilitator; guides/tools for OUD medication and shared decision making	All clinic staff
Leadership engagement	Gain buy-in from executive level of the organization to ensure resources available for QI processes and clinical practice change	1.5-h kick-off meeting with study team and ongoing updates and engagement from external facilitator and champions	Clinic executive leadership
Establish clinic champion(s) and change team	Structured team to conduct QI and change management activities	Executive and clinic leadership select champion(s) with support from facilitator	Identified clinic staff
Training on QI and change management	Improve numeracy, data management, and quality improvement knowledge	45-min web-based training plus external facilitator provides training to champion; champion provide training to change team	Clinic champion(s) and change team
Ongoing QI and change management activities	Improve clinics’ ability to engage in data-driven, structured QI cycles and ongoing data monitoring	Weekly 1-h change team meetings lead by clinic champions and supported by the external facilitator	Clinic champion(s) and change team
eTPA8 client-reported treatment progress tool	Improve clinical outcomes and capacity for technology-based data monitoring and QI	Clients complete the eTPA8 every 2 weeks; staff monitor reports for use in clinical decision making; change team uses reports for QI	All clinic staff, champions, change team

### Measures and materials

#### Data sources

The NYS OASAS registry of all admissions and discharges (irrespective of payer) to licensed addiction treatment facilities—the Client Data System (CDS)—forms the basis of our administrative data set. The CDS will record all treatment episodes that occur in the 30 clinics we include in this study, providing a rich source of data. All licensed providers of SUD treatment in NYS are mandated to submit admission and discharge data into the CDS. NYS OASAS tracks each individual by unique identifiers. When clients enter treatment, providers enter information on demographics, level of functioning (e.g., health status, comorbidities), criminal justice status, recent history and frequency of substance use, and recent SUD treatment history. Upon discharge, providers enter information on functional status (e.g., employment, housing), source of payment for treatment (e.g., self-pay, Medicaid, private insurance), criminal justice involvement during treatment, hospitalizations, and use of ED services. Additionally, the discharge information has type, frequency (i.e., number of sessions), and intensity of SUD treatment as well as discharge status (discharge disposition and goal achievement). NYS Medicaid claims will supplement the administrative dataset by providing data on OUD medications and health services use (e.g., ED visits). We will link clients in Medicaid to the CDS using the NYS OASAS identifier augmented, in cases where there were no exact matches, by searching for same treatment events that were recorded in each database. Additionally, we will employ probabilistic matching techniques to account for data entry errors on elements of the OASAS identifier. Our link rate in previous studies among OUD individuals in Medicaid is 90% [47].

Two additional data sources will represent client-reported outcomes. First, the 8-item eTPA8 will be completed by clients in participating clinics every 2 weeks; data will be retained in the eTPA8 database for analysis. Second, a sample of 40 clients from each clinic will be recruited to complete a survey: 20 clients at the beginning of the intervention and another 20 6 months after the intervention start date at their clinic. Each participant will be assessed three times: (1) at treatment entry, (2) 3 months post-entry, and (3) 6 months post-entry. We will use a mobile platform to collect this data. To recruit clients, clinic staff will present a recruitment flyer to randomly selected newly admitted clients with a primary or secondary OUD diagnosis. The flyer will describe the study and provide a number where they can text to participate. Participants will digitally consent and complete the baseline assessment on their mobile phone. If they do not complete the assessment, they will be sent reminder text messages at 3 and 7 days. Clients will receive a text message with a link to the assessment at each follow-up point, as well as text reminders if they do not complete the follow-ups. Clients will be compensated with a $20 gift card for each assessment.

We will examine staff attitudes, experiences, and behaviors related to implementing CARE with the external facilitator. There will be three data sources: (1) surveys, (2) semi-structured interviews, and (3) external facilitator notes, surveys, and checklists [48]. Online surveys of clinic staff will be administered at baseline and 6 and 12 months post-baseline. All part- and full-time staff will be eligible. Semi-structured interviews will be conducted via phone with at least two clinical and one administrative staff (i.e., clinic director or clinical supervisor) at each of the 30 participating clinics approximately 6 months after starting the CARE intervention or until saturation is reached (no new themes or insights occurring). We will use purposeful, criteria sampling for the interviews to select staff who participated in the change team and/or implementation activities as part of CARE. We will follow best practices for phone-based qualitative interviews in health services [49, 50]. Staff members will provide verbal consent for interviews and digital consent for surveys. In order to inform replication and dissemination of this intervention model as well as to inform on CARE experiences, the external facilitator will complete surveys after each site visit/interaction, monthly narrative reports, and tracking of clinic participation in activities modeled on other facilitation studies [48].

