In this paper, we describe a study protocol for a stepped-wedge randomized controlled trial (SW-RCT) stemming from a state-academic partnership that will test a multicomponent, clinic-level intervention, called Coaching for Addiction Recovery Enhancement (CARE). We will test whether CARE improves treatment process quality and recovery outcomes over treatment as usual, particularly for OUD. The SW-RCT design was selected mainly because the intervention is conducted at the clinic-level and, from a resource perspective, it would be impractical to provide the intervention to all clinics at once given the facilitation model being utilized. Further, the stepped-wedge design was seen as more acceptable and ethical for key program stakeholders (notably the single state agency that regulates SUD treatment [SSA]) due to the potential benefits from the resources being provided as part of the intervention package (e.g., training support from the SSA) compared to a parallel randomization design. The CARE intervention includes the following components: (1) staff clinical training and tools, (2) quality improvement and change management training, (3) external facilitation to support implementation and sustainability of quality improvement, and (4) the eTPA8 client-reported treatment progress tool to support data-driven decision making and clinic-level quality measurement. See Fig. 1 for our intervention conceptual model. We describe intervention components in more detail in the method section. Study aims and hypotheses are the following:
Aim 1: Test the effect of CARE on treatment process quality measures and recovery outcomes.
Hypothesis 1: CARE will improve clinic-level rates of treatment process quality measures (i.e., initiation of and adherence to OUD medications, in-treatment symptom and therapeutic progress, 6-month treatment retention) and recovery outcomes (i.e., substance use, overdoses, self-reported health status, hepatitis C infection [HCV], and emergency department [ED] visits).Aim 2: Examine association of changes in the eTPA8 client-reported treatment progress tool with treatment retention and substance use outcomes.

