### Analysis and power

The primary aim of this study is to test whether CARE is associated with greater use of pharmacotherapy for OUD, longer retention in care, and improved recovery outcomes (e.g., reduced drug use). We will employ multiple convergent analytical methods to (a) examine CARE implementation and (b) test association between CARE and OUD treatment outcomes. Analyses will begin with examination of distributions of variables and transformations where appropriate, examination of patterns of missingness, and application of formal imputation methods [77–79] if deemed essential to project aims. Analyses for Aims 1, 2, and 3 will utilize general linear mixed models (GLMM) for stepped-wedge designs [80–85]. For example, to test the effect of CARE on treatment process quality measures (i.e., initiation and adherence to OUD medications, in-treatment symptom and therapeutic progress, 6-month treatment retention) and recovery outcomes (substance use, overdoses, self-reported health status, HCV infection, and ED visits), we will employ stacked difference-in-difference models that test for within and across clinic changes while adjusting for secular trends across time [80, 86, 87]. The models will take the form: *Y*_*ikt*_ = *μ* + *X*_*kt*_*θ* + *β*_*t*_ + *Z*_*ikt*_ + *α*_*k*_ + *e*_*ikt*_, where *β*_*t*_ is a fixed effect for time, *Z*_*ijk*_ is a matrix of covariates measuring individual, geographical, and clinic characteristics for person *i* in clinic *k* at time *t, X*_*kt*_ is an indicator for intervention in clinic *k* at time *t* (coded 0 for baseline then 1 from when intervention begins in clinic through end of study), and *θ* is the treatment effect. *Y*_ikt_ represents a matrix of binary variables: treatment process quality measures (i.e., pharmacotherapy initiation and adherence, in-treatment symptom and therapeutic progress, treatment retention) and recovery outcomes (i.e., substance use, overdoses, self-reported status, HCV infection, and ED visits). We will estimate the effect of CARE (*θ*) while controlling for secular trends (*β*) and adjusting for clustering within clinic (*α*_*k*_) using robust standard errors. We will also conduct a set of falsification tests. These will include (1) testing for variation in program and client characteristics across time of enrollment; (2) examination of variation across study time in the study outcomes for clinics not participating in the study; and (3) examination of variation in intervention effect based on clinics’ baseline levels of quality measures (e.g., comparing top third to bottom third in quality of care at baseline).

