While there are a number of strengths in this study, we acknowledge the following possible exogenous and endogenous threats to validity. First, administrative data is incomplete. We rely significantly on administrative data to increase the efficiency of our research study that tests the impact of CARE in 30 clinics on treatment quality measures (e.g., pharmacotherapy use, retention) and outcomes (e.g., relapse). While there is strong precedent for using administrative data for research [99–106], these data will not capture all aspects of client experience (e.g., substance use, social consequences). To address the limitation, we are using a mobile platform that allows for collection of research data from a subsample of participants. These data will allow us to further study the intervention impact on recovery outcomes not captured in the administrative data.

In addition, there may be variability in the effect of the intervention due to variation in individual clinic capacity to integrate QI practices within their organizational structure. It will be critically important for future dissemination efforts to understand factors implicated in the implementation of CARE. While the study has adequate statistical power to detect a main effect, it will be important to understand the variability in effect across clinics. To address this, we will incorporate the embedded mixed-methods component of the study examining staff experiences. Additionally, we will explore potential intervention-related factors by conducting a series of post hoc analyses.

Finally, though the SW-RCT design offers a number of benefits, clinics will be randomized to step at the start of the trial with start dates staggered across 3 years. Therefore, it may be challenging to retain recruited clinics in the study while they wait to start the intervention. To reduce clinic attrition, we will employ strategies recommended in the stepped-wedge trial literature (e.g., keep recruited sites informed of progress, hold regular pre-intervention meetings) [107]. Also, recruited clinics will sign a study agreement indicating they understand the randomization procedures and timeline.

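### The client survey has no usual-care follow-up, so the CARE effect on survey-measured substance use and self-reported health cannot be estimated as planned

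*Protocol article*

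**What the plan says.** - **Outcomes.** Hypothesis 1 (Background) expects CARE to improve "recovery outcomes (i.e., substance use, overdoses, self-reported health status, hepatitis C infection [HCV], and emergency department [ED] visits". The article sets the comparison against treatment as usual. Analysis and power repeats the list for the stepped-wedge model: "recovery outcomes (i.e., substance use, overdoses, self-reported status, HCV infection, and ED visits".
- **Exposure.** In that model the intervention indicator X is "coded 0 for baseline then 1 from when intervention begins in clinic through end of study", and θ is its coefficient, with fixed time effects and clustering by clinic.
- **Survey recruitment.** Data sources plans 40 clients per clinic: "20 clients at the beginning of the intervention and another 20 6 months after the intervention start date at their clinic". They are "randomly selected newly admitted clients with a primary or secondary OUD diagnosis", each assessed three times: "1) at treatment entry, (2) 3 months post-entry, and (3) 6 months post-entry".
- **Source of the two outcomes.** Measures puts past 2-week substance use (ASI items) and the first SF-36 item in the mobile survey.
- **Purpose of the survey.** The Discussion concedes that administrative data do not capture substance use, among other things, and says of the survey: "These data will allow us to further study the intervention impact on recovery outcomes not captured in the administrative data".
- **Phases.** Active facilitation occupies the first 6 months of CARE and a sustainment phase the next 6 (Description of the CARE intervention). Five clinics start every 6 months, in 6 steps (Design and participants).

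**The concern.** A stepped-wedge trial estimates its effect by comparing clinic-periods before and after crossover. That needs outcome data from clinics still waiting. The survey opens in each clinic only at that clinic's own CARE start, so waiting clinics supply no survey data to compare with clinics that have crossed over.

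The survey is the article's stated remedy for what administrative data miss. On this schedule it can show how clients fare under CARE, but not whether CARE changes their substance use or self-reported health, which Aim 1 promises to test. The fault lies in data collection, so no later analysis plan could recover the missing control follow-up.

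**Working it through.** **1. The article's own power figure, to check the method.** No detectable difference is given for any survey outcome; the lead figure is 2.8 points for 6-month retention. Inputs from Analysis and power: 30 clinics, 6 steps of 5, m = 132, base rate 0.25, ICC 0.20, alpha 0.01 (taken as two-sided), and 0.80, printed as β, read as power. With T = 7 periods, the Hussey-Hughes variance is

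Var(θ) = Iσ²(σ² + Tτ²) / [(IU − W)σ² + (U² + ITU − TW − IV)τ²]

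- Total variance 0.25 × 0.75 = 0.1875; τ² = 0.20 × 0.1875 = 0.0375; σ² = 0.80 × 0.1875 / 132 = 0.001136.
- U = 105, W = 2,275, V = 455, so IU − W = 875 and the τ² multiplier is 3,500.
- Var = 30 × 0.001136 × 0.2636 / (0.994 + 131.25) = 0.0000680; SE = 0.00824.
- Detectable difference = (2.576 + 0.842) × 0.00824 = 0.0282, matching 2.8 points. That outcome has control-period data.

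**2. Exposure of the planned survey sample.** 30 × 40 = 1,200 clients and 1,200 × 3 = 3,600 assessments. The first cohort's assessments fall at about months 0, 3 and 6 after CARE start, the second's at about months 6, 9 and 12. Under the article's coding, X = 1 for all 3,600.

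**3. Is θ identified?** If adding X to the design matrix leaves its rank unchanged, θ cannot be estimated.

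| Coding of X | Records with X = 0 | Time effects | Time + visit | Time + visit + clinic fixed effects |
|---|---|---|---|---|
| As stated | 0 | 15 → 15 | 16 → 16 | 45 → 45 |
| All of cohort 1 set to 0 | 1,800 | 15 → 16 | 16 → 17 | 45 → 45 |
| Only cohort 1's entry assessment set to 0 | 600 | 15 → 16 | 16 → 17 | 45 → 46 |

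The first row has no solution for θ. The second contradicts the stated coding, and cohort 1's 3- and 6-month outcomes still arise during active CARE, so its coefficient is early versus later CARE. In the third, every unexposed record is an admission value; once visit is in the model, it compares clients admitted at CARE start with clients admitted 6 months later.

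**4. Other sources.** The Client Data System records frequency of use and health status at admission, but neither is among the listed discharge items, and Measures uses frequency of use as a covariate. The eTPA8 is a CARE component, and no control-phase administration is described.

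**5. What a re-timed survey could detect.** Layout: 20 control clients per clinic in the period before crossover (steps 2 to 6) and 20 CARE clients per clinic one period after start, with period effects and a random clinic intercept. Assumed outcome rate 40%, 80% power, two-sided tests, no loss to follow-up.

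| ICC (assumed) | SE | Detectable difference, alpha 0.05 |
|---|---|---|
| 0.02 | 0.038 | 10.5 points |
| 0.05 | 0.042 | 11.7 points |
| 0.10 | 0.048 | 13.4 points |
| 0.20 | 0.058 | 16.2 points |

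At the article's alpha 0.01 and ICC 0.20 it is (2.576 + 0.842) × 0.058 = 19.8 points. With clinic fixed effects, θ is still aliased in this layout (rank 35 → 35).

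**6. Lead time.** About 2,000 clients per year over 30 clinics is 5.6 per clinic per month; the eligibility minimum of 50 per year is 4.2. If every client were a new admission and consented, 20 clients take 20/5.6 = 3.6 to 20/4.2 = 4.8 months. Adding 6 months of follow-up, enrolment must open roughly 10 to 11 months before crossover.

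**The case against.** The strongest defence is that the first cohort is meant as a baseline. It enters at the start of CARE, not after it, and its treatment-entry assessment may be close to pre-exposure. A reader might infer that both cohorts are recruited once CARE is under way, or that the survey supports no contrast at all. The article does not support either reading: the entry assessment is a fair near-baseline admission value, and early and later CARE clients can be compared. But that is not the effect in Hypothesis 1, and no 3- or 6-month outcome is observed under usual care.

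A second defence is scope. Every outcome in the power paragraph is administrative, and the Discussion describes the survey as covering a subsample. This stands as a limit. Retention comes from the Client Data System, and medication, overdose, hepatitis C and emergency department outcomes from Medicaid claims; both sources cover control periods. A reader might infer that Aim 1 as a whole fails, and it does not.

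A third point concerns the remedy. Moving the first cohort has real costs in precision, lead time and Aim 2 data. Those costs stand and are set out under the fix, but they do not repair the schedule as written.

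**Conclusion.** The point holds for the two survey-measured recovery outcomes, substance use and self-reported health. As scheduled, 0 of 1,200 survey clients have X = 0, no follow-up is observed under usual care, and θ is not identified. That conclusion rests only on the stated recruitment times, the stated coding and the survey being the sole described outcome source; it needs no assumption about rates or ICC.

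Saying that no coding of X can yield an estimate would go too far. Recoding the first cohort as unexposed gives an estimable coefficient under random clinic effects, but it measures early against later CARE. The detectable differences for a re-timed survey are illustrations: the 40% rate and the survey ICCs are assumptions, and the layout matters. Placing the CARE cohort in the first CARE period instead gives about 8.8 to 11.0 points at alpha 0.05 for ICC 0.01 to 0.30.

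**What to change.** **Preferred change.** Move the first 20 survey clients per clinic into the control phase wherever the randomised start allows. Open enrolment early enough (accrual time plus 6 months) that the 3- and 6-month assessments end before crossover. Keep the second 20 in the CARE phase. Analyse with period effects and a random clinic intercept, and state that θ then rests partly on between-clinic information and is aliased under clinic fixed effects.

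**What it costs.**
- Step 1, and probably much of step 2, which starts only 6 months later, would supply little or no control data.
- With no step-1 control clients, the total is 25 × 20 + 30 × 20 = 1,100, not 1,200, unless those places are reallocated.
- If the eTPA8 is not used in the control phase, survey clients with eTPA8 data for Aim 2 fall by about half, from 1,200 to 30 × 20 = 600.
- The early-CARE survey cohort is lost.
- Precision is limited, so the plan should state a detectable difference for the survey outcomes with its assumptions.

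**If re-timing is not possible.** Remove substance use and self-reported health from the outcomes on which θ is estimated, in Hypothesis 1 and in Analysis and power. Amend the Discussion statement about studying intervention impact, and report the survey as an early-versus-later CARE comparison plus Aim 2. This costs no data, but gives up a usual-care comparison for these outcomes.
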